## Abstract

**Background:**

Mechanical ventilation (MV) is essential in the management of critically ill neonates, especially preterm infants. However, inappropriate or prolonged use of invasive MV may result in ventilator-associated lung injury. A systemic review comparing pressure control ventilation (PCV) with volume-targeted ventilation mode (VTV) approved that VTV reduces the incidence of death or bronchopulmonary dysplasia (BPD) in neonates; however, this study did not analyze subgroups of very low birthweight (VLBW) infants. Therefore, the aim of this study was to compare the use of VTV and PCV in VLBW infants and to provide clinical evidence for reducing mortality and complications of MV in VLBW infants.

**Method:**

A single-center randomized controlled trial will be performed. All eligible infants will be randomized and assigned to either VTV or PCV group with 1:1 ratio using sealed envelopes. Death or BPD at 36 weeks’ postmenstrual age will be used as the primary outcome. Secondary outcomes include BPD, death, length of invasive MV, noninvasive mechanical ventilation, and oxygen use, length of hospital stay, failure of conventional MV, rate of using high-frequency oscillatory ventilation (HFOV) as rescue therapy, rate of reintubation within 48 h, and hospital expenses.

**Discussion:**

Systemic review suggested that VTV decreases the incidence of death or BPD in neonates compared to PLV; however, this study did not specifically analyze subgroups of VLBW infants. We designed this single-center randomized controlled trials (RCT) to add a significant contribution regarding the benefits of VTV for VLBW patients.

**Supplementary Information:**

The online version contains supplementary material available at 10.1186/s13063-023-07564-x.

## Introduction

Mechanical ventilation(MV) is essential in the management of critically ill neonates, especially preterm infants. Seventy-six percent of preterm infants at 26–28 weeks of gestational age require invasive MV; 33% and 16% of preterm infants at 29–32 weeks and 33–34 weeks of gestational age, respectively, require invasive MV. However, inappropriate or prolonged use of invasive MV may result in ventilator-associated lung injury [1, 2] and be associated with the high risk of bronchopulmonary dysplasia (BPD) [3–5]. Therefore, it is important to select a better ventilation mode for neonates.

Pressure control ventilation (PCV) or sometimes called pressure limited ventilation (PLV) is an effective mode for newborn infants who need respiratory support. Each breath is delivered with a preset peak inspiratory pressure (PIP), which prevents barotrauma caused by high pressure. However, tidal volume (Vt) is varied with patient’s inspiratory effort, lung compliance, and airway resistance. Actual delivered Vt appears to be too large or too small, resulting in over- or under-ventilation in the mode of PCV [6].

Volume-guaranteed (VG) ventilation is a type of volume-targeted ventilation mode (VTV), which can automatically adjust the inspiratory pressure within the set maximum pressure, in order to deliver Vt based on the pre-set target Vt [7]. In VTV, actual Vt stays relatively stable to better stabilize the partial pressure of carbon dioxide(PCO_2_) [8, 9]. When the infants’ lung condition improves, the ventilator weans the inspiratory pressure downward in real-time according to the target Vt to reduce the mean airway pressure(MAP), thus reducing the length of MV [10].

An international survey published in 2011 found that the use of VTV in neonates is gradually increasing. Approximately 50% of the included institutions use VTV as their routine mode [11]. Nevertheless, the clinical use of VTV in neonates varies in different countries. A survey of neonatologists in Canada and the USA published in 2019 found that the use of VTV was higher than in Canada (81%) than in the USA (39%). And the main reasons for not using VTV was “lack of understanding” [12].

A 2017 Cochrane review of 20 randomized controlled trials (RCT) comparing PLV with VTV in 1065 neonates approved that VTV reduces the incidence of death or BPD in neonates [10]; however, this study did not analyze subgroups of very low birthweight (VLBW) infants. A meta-analysis found that the use of VTV did not increase in adverse events, suggesting that the use of VTV in extremely low birthweight (ELBW) is safe [13].

In the latest 20 years, evidence about VTV as primary respiratory support in VLBW is few. One study reported that using VTV in infants with birthweights of 500–1249 g did not alter time to extubation [14]. However, this study was done in 2005. Another RCT with small sample size found that VTV decreased combined outcome of BPD or death [15]. More high-quality clinical evidence of VTV is needed. Therefore, the aim of this study was to compare the use of VTV and PCV in VLBW infants and to provide clinical evidence for reducing mortality and complications of MV in VLBW infants.

## Methods: participants, interventions and outcomes

### Objective

The objective is as follows: to investigate the effects of VTV and PLV as a respiratory support mode on BPD/death in VLBW infants.

### Study design

A single-center randomized controlled trial will be performed. Patients will be randomized in two parallel groups: VTV vs PCV in 1:1 ratio. The study type was a superiority study to verify the use of VTV over PCV in VLBW infants.

### Inclusion criteria

Infants satisfying the following inclusion criteria will be eligible to participate:Admitted for admission to neonatal intensive care unit, andBirthweight < 1500 g, andInfant need invasive mechanical ventilation.

### Exclusion criteria

Infants with the following exclusion criteria will not be eligible to participate:Fatal congenital malformations or chromosome abnormality found before or after randomization, orDiaphragmatic hernia, meconium aspiration syndrome, and air leak syndrome, orHigh-frequency oscillatory ventilation (HFOV) or any other invasive mode has been used before, orRefusal to participate in the trial.

### Sample size

An RCT of VLBW infants with respiratory distress syndrome(RDS) receiving VTV or PCV as their primary respiratory support mode showed that the BPD/death rate of 26% and 64% respectively [15]. Based on this study, a sample size of 31 in each group will have 90% power to detect statistically difference at a 0.05 tow-sided significance level (MedSci, Shanghai, China). Considering a 20% of patients may withdraw from the research, a sample size of 68 will be appropriate.

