### Primary outcome

Death or BPD at 36 weeks’ postmenstrual age will be used as the primary outcome. BPD will be diagnosed by clinical physicians. The definition and diagnostic criteria of BPD is according to NIH 2018 [16]. We have chosen “death or BPD (36w)” as our primary outcome to maintain similarity with previous trial comparing VTV and PCV [10].

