## Trials status

Version number: 3, 2023 March 01.

This trial started recruiting patient since 2023 May 01. Sixty-eight infants will be recruited over 1 year. The trial will terminate when the last recruited infant is discharged from the hospital or dies.

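### The enrolment target of 68 allows for about 9% loss, not the stated 20%; if 20% of infants have no primary outcome, power is about 86%, not 90%

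*Protocol article*

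**What the plan says.** The primary endpoint is binary: "Death or BPD at 36 weeks’ postmenstrual age will be used as the primary outcome" (Primary outcome). The Sample size section of the protocol article takes its event rates from one earlier trial, which "showed that the BPD/death rate of 26% and 64% respectively" for VTV and PCV. It states that "a sample size of 31 in each group will have 90% power to detect statistically difference" "at a 0.05 tow-sided significance level". The next sentence moves to the enrolment figure: "Considering a 20% of patients may withdraw from the research, a sample size of 68 will be appropriate". Trials status repeats that figure as the recruitment target: "Sixty-eight infants will be recruited over 1 year". Allocation is 1:1 (Study design), so 68 means 34 per group.

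No section gives a withdrawal rate below 20% or shows how 62 became 68.

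**The concern.** The section makes two linked claims: that 62 infants with an outcome are needed for 90% power, and that enrolling 68 protects this number against 20% withdrawal. An allowance for withdrawal has a purpose only if withdrawn infants supply no outcome. On that premise, 68 infants less 20% fall short of 62, so the two claims cannot both hold.

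What is at stake is how the result is read. If the trial loses outcomes at the rate it planned for and finds no significant difference, readers would set that finding against a chance of missing the assumed effect of 10%, when the chance is higher. Type I error, the effect estimate and the validity of its confidence interval are not affected.

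**Working it through.** **Inputs, all from the protocol article.** Event rates p1 = 0.26 (VTV) and p2 = 0.64 (PCV), difference 0.38; two-sided alpha 0.05; power 90%; 31 per group; 20% withdrawal; 68 enrolled (Sample size). Allocation 1:1 (Study design).

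**Step 1: reproduce the plan's 31.** With the unpooled variance,

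n per group = (z0.975 + z0.90)² × [p1(1 − p1) + p2(1 − p2)] / (p1 − p2)²

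= (1.960 + 1.2816)² × (0.1924 + 0.2304) / 0.1444 = 30.8, rounded up to 31.

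The stated 31 is therefore correct on this formula. The pooled-variance formula gives 33.9, rounded up to 34. Both are standard, and the section does not name the one used. The unpooled formula is the main basis below because it returns the plan's own number.

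**Step 2: the withdrawal allowance.**

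- Needed with an outcome: 2 × 31 = 62.
- Enrolment to keep 62 after 20% loss: 62/0.8 = 77.5, so 78 (39 per group).
- The common but incorrect shortcut, 62 × 1.2 = 74.4, gives 75, which is also not 68.
- Loss that 68 can absorb: 1 − 62/68 = 8.8%.
- Left from 68 after 20% loss: 68 × 0.8 = 54.4, about 27 per group against the required 31.

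**Step 3: power at each number with an outcome.** Unpooled: power = Φ(0.38 / √(0.4228/n) − 1.960), where 0.4228 = 0.1924 + 0.2304. At n = 27 this is Φ(3.037 − 1.960) = Φ(1.077) = 0.859. The pooled figures use the same rates and alpha.

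| Infants with an outcome, per group | Situation | Unpooled | Pooled |
|---|---|---|---|
| 34 | 68 enrolled, none lost | 92.6% | 90.1% |
| 31 | 68 enrolled, about 9% lost | 90.2% | 87.1% |
| 27 | 68 enrolled, 20% lost | 85.9% | 82.0% |

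The columns should be read downwards. Taking the 90% from one and the 82% from the other would mix the choice of formula with the effect of loss. From 31 to 27 per group, the shortfall is about 4 points unpooled (90.2 − 85.9 = 4.3) and about 5 points pooled (87.1 − 82.0 = 5.1).

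**The case against.** The strongest reply is that withdrawal, as this protocol defines it, is not the same as a missing outcome. The Definitions section counts non-respiratory deaths and early discharges as withdrawals. Death from any cause is part of the primary endpoint, and Statistical methods plans efficacy analyses by intention to treat. An infant withdrawn through death before 36 weeks therefore has a known primary outcome, and other withdrawn infants may have one too. If every outcome is known, all 68 are analysed and power is at least 90% on either formula.

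This stands as a limit on the consequence: 27 per group is the worst case, not the expected number. It does not repair the sentence. If withdrawn infants are all analysed, no inflation is needed; if none are, 78 are needed. Neither reading leads from 62 to 68 through 20%. Nor is the loss safely zero: early discharge at the family's wish is also a withdrawal, outcomes are collected before discharge (Data collection), and an infant who leaves before 36 weeks may have no BPD assessment.

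A second reply is that about 4 points of power is little. That is fair on the plan's own basis, and it argues for a plain correction, not for a redesign.

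**Conclusion.** The inflation step is wrong as stated. The figure of 31 per group reproduces, but 68 covers about 8.8% loss where the section claims 20%. If 20% of infants contribute no primary outcome, power is about 86% on the formula that gives the plan's 31, so the chance of missing the assumed effect is about 14% instead of 10%. These figures assume the plan's event rates of 26% and 64%, two-sided 0.05 and equal loss in both groups.

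Three stronger readings are not supported:

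- A reader might infer that the trial simply lacks 90% power. The protocol attaches 90% to 31 per group, where it holds on the unpooled formula. It is lost only if more than about 9% of the infants have no outcome.
- A reader might quote a larger shortfall from Fisher's exact test. Statistical methods plans risk differences with confidence intervals and logistic regression, and does not mention that test.
- A reader might guess how 68 arose, for example as the pooled-formula size with no allowance or as a 10% allowance. The document does not say, and the point does not depend on it.

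**What to change.** Restate the last two sentences of the Sample size section on one named formula, for example:

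> 68 infants give 90% power (unpooled normal approximation, 26% vs 64%, two-sided 0.05) if no more than about 9% have no primary outcome; if 20% have none (27 per group), power is about 86%.

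If the sponsor prefers the pooled formula, the matching figures are 90% with no loss, 87% at 31 per group and 82% at 27 per group. Expressing the allowance as infants without a primary outcome, and not as withdrawals, also removes the ambiguity left by the Definitions section.

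The cost is one corrected passage, carried into the final report, and a slightly less favourable stated power under 20% loss. The target of 68 in Trials status can stay. Enrolling 78 would keep both the 20% and the 90%, but it is not needed to correct the statement. It is the sponsor's choice and, as a change of sample size, would need the formal amendment described under Protocol amendments.

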### Recruitment

This study will be implemented in West China Second Hospital, a teaching hospital in Chengdu, China.

After admission of all infants who might meet the eligibility, a written informed consent will be explained to at least one parent or legal guardian by the principal investigator or delegated deputy. Informed consent will be signed by at least one parent or legal guardian. All patient admitted in our neonatal intensive care unit (NICU) will be screened. Based on patient in-charged in 2022, we anticipate 1 year to recruit enough patients. This time might be prolonged or shortened due to different reasons. A senior investigator will be available at all times to discuss concerns raised by parents or clinicians during the course of the trial.

## Assignment of interventions: allocation

Randomization will be immediately performed once the eligibility is confirmed. All eligible infants will be randomized and assigned to either VTV or PCV group with 1:1 ratio. Stratified randomization will be done according to a computer-generated random number and variable block sizes (2) will be used to strengthen allocation concealment. Multiple birth infants will be randomized separately. Randomization will be stratified by birthweight (< 1000 g versus > / = 1000 g).

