### Implementation

The second author will generate the allocation sequence. All authors will participate in enrolling and assigning participants. The names of the treatment groups were placed into envelopes per the randomization sequence, sealed, and labeled with a sequential participant number. Once a patient consented to participate, a researcher who is on call that time will open the envelope to reveal the name of the assigned group.

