## Assignment of interventions: blinding

Both of the modes have parameter adjustment on the ventilator; respiratory therapists and attending physicians will not be blinded due to the nature of the study. Blinding was set for the remaining study personnel like statistician, patients, and families. There will be no circumstances under which unblinding is permissible, as the respiratory therapists will not be blinded due to the nature of the study and family members are not allowed to get into the NICU due to the hospital policy. To minimize bias, “ventilator adjusting protocol” and “criteria for extubation” have been carefully defined and adhered.

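### One listed block size of 2, and a sequence generator who also recruits, leave allocation open to prediction

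*Protocol article*

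**What the plan says.** Under *Assignment of interventions: allocation*, the article states a 1:1 ratio and two strata split at a birthweight of 1000 g. It says that "variable block sizes (2) will be used to strengthen allocation concealment". It adds that "Multiple birth infants will be randomized separately".

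Under *Implementation*: "The second author will generate the allocation sequence. All authors will participate in enrolling and assigning participants". Group names were put into sealed, sequentially numbered envelopes, and the on-call researcher opens one after consent. The article does not say who filled the envelopes or who keeps the list.

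Under *Assignment of interventions: blinding*: "respiratory therapists and attending physicians will not be blinded due to the nature of the study". *Study design* gives one centre.

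**The concern.** The allocation sentence contradicts itself: it promises variable sizes, names one, and claims that this strengthens concealment. If the size is 2, the effect is the reverse. At 1:1, the second infant of each pair always gets the mode that the first did not, and the mode is visible on the ventilator. Stratification gives no cover, because birthweight is known and each stratum can be followed separately. If two siblings in one stratum are enrolled one after the other and the first opens a block, the second sibling's arm is certain. The block size is also in print.

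The overlap of roles is a second and independent weakness, which stands whatever the block size. The person who produces the sequence also recruits, and the article states no barrier between the two tasks.

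What is at stake is the comparability of the arms at entry. Entry depends on a judgement that the infant needs invasive ventilation (*Inclusion criteria*), and consent is sought by the principal investigator or a deputy (*Recruitment*). Someone who foresees the next arm could let that influence whether, or when, an infant is entered.

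**Working it through.** The article gives no figure for predictability, so there is none to reproduce.

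**Inputs.** Ratio 1:1, block size 2 and two strata (*allocation*); 68 infants (*Sample size*); planned event rates 26% and 64%, a difference of 64 − 26 = 38 points (*Sample size*). How the 68 divide between strata is not stated, so splits of 34/34, 20/48 and 23/45 were tried as assumptions.

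**Blocks of 2.** The observer is assumed to know the earlier allocations in the stratum.
- First of a pair: a 50/50 guess. Second of a pair: certain.
- Certain allocations with even strata: 34/2 + 34/2 = 34 of 68 = 50%.
- With odd strata (23/45): 11 + 22 = 33 of 68 = 48.5%.
- Best-guess rate: 0.5 × 1 + 0.5 × 0.5 = 75%. With odd strata: (33 + 35 × 0.5)/68 = 74%. Simple randomization would give 50%.

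**Other schemes.** These were simulated with 2,000 repetitions for each split. The observer knows which sizes are possible but not their order, and updates the probabilities after each allocation.

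| Blocks | Certain | Best guess right |
|---|---|---|
| 2 only | 49–50% | 74–75% |
| 4 only | 31–33% | 70–71% |
| 2 and 4, concealed | about 11% | about 72% |
| 4 and 6, concealed | about 6% | about 69% |

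The third row covers the reading in which the figure 2 counts sizes rather than naming one. Withholding the sizes does much of the work: with 4 and 6, about 27% would be certain if the block boundaries were known.

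**Possible bias.** With pairs, about half of each arm sits in a predictable slot. Suppose selection lowers baseline risk by *a* points in the predictable VTV slots and raises it by *b* points in the predictable PCV slots. The false difference is then 0.5*a* + 0.5*b*.
- No steering: 0 points.
- 10 points in one arm only: 0.5 × 10 = 5 points, or 5/38 = 13% of the planned difference.
- 10 points in both arms, in opposite directions, in every predictable slot: 5 + 5 = 10 points, or 10/38 = 26%.

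The 10 points are an assumption. Nothing in the article supports that value or any other.

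**The case against.** The article never says that the blocks are fixed. The figure 2 may count sizes, or a second size may have been lost when the full protocol was condensed. This stands to the extent that the 50% is conditional. The sentence needs correcting on any reading.

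Certainty also requires tracking of earlier allocations in a stratum, which is plausible in one NICU but not automatic among rotating on-call researchers. This stands too.

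There are real safeguards. All NICU admissions are screened, randomization follows at once when eligibility is confirmed, and envelopes are sealed, numbered and opened only after consent. Prior use of another invasive mode excludes an infant, which leaves less room to hold one back for a later slot. These measures limit steering, but none prevents deduction from the preceding allocation. The prior-mode exclusion also means that starting another mode first takes the infant out of the trial.

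A reader might infer three stronger things that the article does not support:
- That a recruiter does know the whole list. It says who generates the sequence, not who keeps it.
- That a false difference of 10 points is to be expected. That figure needs opposite steering in every predictable slot of both arms.
- That no analysis could help. *Statistical methods* plans multivariable regression if prespecified baseline characteristics are unbalanced, and prognostic factors such as gestational age and antenatal steroids are recorded. This can reduce bias from measured factors but cannot reach unmeasured selection.

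**Conclusion.** The concern holds as a weakness in concealment with a conditional size. Two things are certain from the text: the block statement contradicts itself, and sequence generation is not separated from enrolment and assignment. If all blocks are of size 2 and staff know the earlier allocations in a stratum, about half of allocations (33 or 34 of 68) can be deduced and about 75% guessed. If two concealed sizes such as 2 and 4 were meant, about 11% can be deduced.

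The result is an opportunity for selective enrolment that sealed envelopes do not close and that the planned adjustment can only partly address. It does not show that selection occurred. The 5 to 10 points of bias illustrate what a 10-point shift in the predictable slots of one or both arms would do; they are not an estimate. Correction is still warranted, because the primary comparison relies on concealment and the scheme as written works against its own stated aim.

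**What to change.** For the remaining sequence, use randomly varying blocks of 4 and 6 within each birthweight stratum, beginning after a completed pair. Keep the sizes out of any document that recruiters can see. Remove the sequence generator from enrolling and assigning, and state who prepares the envelopes and holds the list. Correct the block sentence.

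The main gain is in certain allocations, which fall from about 50% to about 6%. The best-guess rate falls only from 75% to about 69%.

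The cost is a new list and envelopes, an amendment by the route under *Protocol amendments*, and a possible end imbalance of up to 3 infants per stratum (half of an unfinished block of 6). No extra staff are needed.

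Recruitment began on 2023 May 01 and was planned for one year, so there may be no sequence left to change. In that case, report the block sizes actually used and who had access to the list.
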